## Abstract

**Background:**

Lack of patient involvement in decision making has been suggested as one reason for limited treatment success. Concepts such as shared decision making may contribute to high quality healthcare by supporting patients to make informed decisions together with their physicians.

A multi-component shared decision making programme on the prevention of heart attack in type 2 diabetes has been developed. It aims at improving the quality of decision-making by providing evidence-based patient information, enhancing patients’ knowledge, and supporting them to actively participate in decision-making. In this study the efficacy of the programme is evaluated in the setting of a diabetes clinic.

**Methods/Design:**

A single blinded randomised-controlled trial is conducted to compare the shared decision making programme with a control-intervention. The intervention consists of an evidence-based patient decision aid on the prevention of myocardial infarction and a corresponding counselling module provided by diabetes educators. Similar in duration and structure, the control-intervention targets nutrition, sports, and stress coping. A total of 154 patients between 40 and 69 years of age with type 2 diabetes and no previous diagnosis of ischaemic heart disease or stroke are enrolled and allocated either to the intervention or the control-intervention. Primary outcome measure is the patients’ knowledge on benefits and harms of heart attack prevention captured by a standardised knowledge test. Key secondary outcome measure is the achievement of treatment goals prioritised by the individual patient. Treatment goals refer to statin taking, HbA1c-, blood pressure levels and smoking status. Outcomes are assessed directly after the counselling and at 6 months follow-up. Analyses will be carried out on intention-to-treat basis. Concurrent qualitative methods are used to explore intervention fidelity and to gain insight into implementation processes.

**Discussion:**

Interventions to facilitate evidence-based shared decision making represent an innovative approach in diabetes care. The results of this study will provide information on the efficacy of such a concept in the setting of a diabetes clinic in Germany.

**Trial registration:**

ISRCTN84636255

## Background

Cardiovascular disease is the predominant life threatening complication associated with type 2 diabetes. An array of behavioural directives, such as quitting smoking, increasing exercise, normalising weight, and adhering to monitoring, dietary and medication prescriptions is imposed on patients with type 2 diabetes. Evidence on efficacy of these measures is varying and some may even do more harm than good [1]. Patients frequently feel demotivated and overloaded by the plethora of medical prescriptions. This might contribute to poor long-term adherence [2,3] even to the most effective preventative interventions such as blood pressure control [4] and use of statins [5].

International and national societies claim a “patient centred approach” such as shared decision making (SDM) in diabetes care [6,7]. SDM [8] implicates an “involvement of both the patient and the doctor, sharing of information by both parties, taking steps to build a consensus about the preferred treatment, and reaching an agreement about which treatment to implement” [9]. A prerequisite for an informed decision making process is evidence-based patient information [8,10]. In Germany however, SDM has not yet been implemented in diabetes care. Current education and counselling programmes for patients with diabetes provide rather general information, without numerical and comparative risk information [11-14].

Key objective of this project is to improve the quality of decision-making by enhancing patients’ understanding and supporting them to actively deliberate between the available treatment options. This approach is implicated by the theory of planned behaviour [15], according to which behaviour is influenced by attitudes, by subjective norms such as perceived physicians’ attitudes, and by perceived and actual individual behaviour control. Providing evidence-based information aims at strengthening behaviour control by resolving knowledge deficits. Information about probabilities of outcomes is tailored to individual risk to realign unrealistic expectations.

An informed shared decision making (ISDM) programme on the prevention of heart attack in type 2 diabetes has been developed [16,17]. In terms of a complex intervention [18], it includes a number of interdependent components that may interact with contextual factors such as the educational background of participants and the setting. Development and evaluation of these components encompassed theoretical and empirical groundwork focusing on in-depth understanding of contextual interactions and implementation processes. Details are published elsewhere [16,17,19-21].

Key component of the ISDM-programme is an evidence-based patient decision aid (DA) [17]. The DA comprises decision relevant information on the concept of benefits and harms of different preventative options, an individual risk assessment tool, and a guide to support the decision making process. A preliminary qualitative study with diabetes educators and patients [17] indicated good acceptance and suitability to support informed decision making. Implementation of the DA is considered as optimal within patient education curricula and counselling programmes. Therefore, a patient counselling module was developed [16] related to the DA (updated 08/2012) and based on current criteria of evidence-based patient information [10]. In order to simplify implementation, duration and structure have been adapted to current patient education modules [11,12]. The counselling module was piloted within the target group and iteratively optimised [16]. In order to enable diabetes educators to successfully apply the counselling, a train-the-trainer module has been developed, consisting of a video with examples and instructions, and a structured training-session.

Since piloting of the components of the ISDM programme demonstrated feasibility and acceptance, evaluation of the efficacy of the programme in a randomised-controlled trial (RCT) is required prior to implementation [18]. In addition, concurrent qualitative research is needed to monitor and to ensure reliability and validity of the intervention [22].

The reporting of this study follows current statements [23-25].

## Objectives

Primary objective is to investigate if the ISDM programme is superior to the control-intervention regarding patients’ knowledge and realistic expectations concerning benefits and harms of the available treatment options. Key secondary objective is to determine if patients in the ISDM group achieve their individual treatment goals better than patients in the control-group. Additional objectives are to assess if patients presenting high numeracy levels achieve better knowledge than patients presenting low numeracy, if social status correlates to the level of knowledge, and if patients with good knowledge achieve their treatment goals better than patients with poor knowledge.

## Methods

### Design

A parallel group, two-arm, single blinded, randomised-controlled, superiority trial with 6 months follow-up is conducted under high fidelity intervention conditions [22] comparing the ISDM programme with a control-intervention. Concurrent qualitative methods are used to explore and promote intervention fidelity [22] and to achieve in-depth understanding of implementation processes.

### Setting

Study site is the diabetes clinic at the Department for Endocrinology and Metabolic Diseases of the Jena University Hospital, Germany. In this clinic, patients are followed by diabetes educators and physicians usually twice but at least once a year. Most patients have joined a structured treatment and teaching schedule within the disease management programme (DMP). Four diabetes educators guide, motivate, and coach the patients in individual and group counselling sessions. Integral to the multidisciplinary diabetes care team, the educators develop individual plans of care, provide on-going self-management support, and analyse and adapt diet-sheets and insulin dosages. Patient characteristics, diagnoses, laboratory parameters, and prescriptions are documented in an electronic patient record system (EPRS).

### Eligibility and recruitment

Patients with type 2 diabetes between 40 and 69 years of age are eligible for enrolment if they have no previous diagnosis of ischaemic heart disease (ICD I20-I25) or stroke (ICD I63) and have participated in the DMP education programmes for patients with type 2 diabetes. Patients are eligible with HbA1c-values between 6 and 9%. This range of values is sensitive to patient participation in decision making, regarding micro-vascular prevention. Patients are excluded if they have proliferative retinopathy, chronic kidney disease stage 3 or higher [26], metastatic cancer, or are addicted to alcohol or cared by a legal guardian.

EPRS is screened for eligible patients (study flow Figure 1). Those are asked to participate during their regular consultation. The first patient was enrolled in March 2013. Estimated completion of recruitment is December 2013.

**Figure 1 F1:**
[figure not shown]
Study flow.

### Randomisation and blinding

Randomisation is performed in blocks of 8 to ensure close balance of numbers of participants in each group and sufficient numbers of participants (n = 4) in each counselling session. Randomisation sequence is generated independently by the Centre for Clinical Studies at the Jena University Hospital.

Patients are blinded to study group allocation. Allocation is concealed during data entry and analysis.

### Study interventions

#### Intervention group (ISDM programme)

The intervention (Table 1) comprises a decision aid booklet [17] and a corresponding counselling module. The counselling is provided by diabetes educators of the participating clinic. Patients are guided through the decision making process, by 1) jointly assessing the patient’s individual heart attack risk, 2) providing outcome probabilities of the available preventative treatment options, and 3) supporting to set individual goals regarding smoking cessation, glucose control, blood pressure control, and statin treatment. A physician is to be consulted if patients wish a change of treatment regimens.

**Table 1 T1:** Characteristics of intervention and control intervention

	**ISDM programme**	**Control-intervention**
**Components**	Decision aid booklet “On the prevention of heart attack in type 2 diabetes” [17]	Brochure “Stress” [27]
	Curriculum	Curriculum
	Media: Specific wall charts, worksheets, question cards, and a magnet board	Media: Specific wall charts, worksheets, and a relaxation exercise
**Duration**	60-90 minutes	60-90 minutes
**Group size**	4 participants	4 participants

The counselling module takes about 90 minutes. Patients are asked to read and work through the DA, at least one week before the group counselling session.

For study purposes, two diabetes educators have attended the ISDM programme specific train-the-trainer module given by a research fellow of the Unit of Health Sciences and Education of the University of Hamburg. In order to ensure educational fidelity, certified diabetes educators provide the counselling sessions. To ensure fidelity of the evidence-based contents, the sessions are videotaped and analysed. If required, the research fellow gives feedback for optimisation.

#### Control group

Framing, duration and structure of the control-intervention are similar to the ISDM intervention (Table 1). In contrast to the ISDM intervention, participants are guided through a counselling session about nutrition, sports, and stress coping. The session ends after a take home relaxation exercise. At least one week before the session, all participants receive a brochure on stress management offered by health insurances [27].

### Outcomes

Primary outcome measure (Table 2) is the level of patient knowledge relating to the concept of risk, the notion of heart attack risk, and the benefits and harms of preventative treatment. Knowledge is captured by a standardised questionnaire consisting of 12 questions to assess *comprehension of risk information* and *realistic expectations*[28], plus one question to assess *numeracy*[29].

**Table 2 T2:** Data collection

**Outcomes**	**Measures**	**No. of items**	**Follow-up**^ ***** ^
Knowledge	• Questionnaire developed on the basis of Bloom’s taxonomy [30] and evidence-based information on heart attack prevention in type 2 diabetes [17] (updated 08/2012)	13	T1, T2
Realistic expectations	• Questionnaire developed on the basis of ISDM-counselling	6^**^	T1, T2
Numeracy	• Numeracy test (one minute test for general population) [29]	1^***^	T1
Treatment goals	• Statin medication, levels of blood pressure and glucose control, smoking, and patient’s prioritized treatment goal are documented on a standardised form	1 for each goal	T1
Achievement of treatment goals	• Statin medication (patient medication boxes)	1	T2
	• Blood pressure (self-monitoring, standardised measure if not available)	1	T2
	• HbA1c-level (standardised measure)	1	T2
	• Smoking cessation (question by diabetes educator)	1	T2
Medication	• Variation in medication intake (statins, antihypertensive drugs, glucose-lowering agents) are documented using medical records (T1) and by verifying patients’ pill-packages (T2).	3	T1, T2

^*^ T1; at the end of the counselling session; T2; at 6 months follow-up.

^**^ 6 out of 13 questions of the knowledge test.

^***^ 1 out of 13 questions of the knowledge test.

Secondary outcome measures comprise 1) sustainability of knowledge; 2) achievement of individual treatment goals regarding the use of statins, levels of blood pressure and glucose control, and smoking; 3) achievement of treatment goals prioritised by the individual patients; 4) medication uptake from T1 to T2.

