### Data collection

The EPRS of the clinic and standardised forms are used to collect baseline characteristics and outcome measures.

Baseline characteristics include age, gender, first-language, social status [31], smoking status, blood pressure, LDL-cholesterol, total cholesterol, HbA1c, current medication, and previous participation in diabetes patient education programmes.

Baseline risks of myocardial infarction are calculated by using a risk assessment tool based on age, smoking status, and clinical parameters. The tool is derived from the Framingham function and calibrated [32] to the average heart attack risk in the German population.

Knowledge is assessed directly after the counselling session and at 6 months follow-up. The individual treatment goals regarding smoking cessation, glucose control, blood pressure control, and statin treatment are assessed after the counselling session. Achievement of treatment goals is assessed during a consultation at 6 months follow-up. Current medication is monitored by verifying patients’ pill-packages. Smoking status is assessed by using a standardised interview question. Current blood pressure values (mean of 2 weeks) are extracted from patient diaries. If values are not available, blood pressure is measured before counselling by a nurse applying a standardised procedure (after 5 minutes seated position). Glucose control is assessed by measuring HbA1c-levels [33].

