#### Secondary outcomes

Unpaired t-tests will be used to compare mean knowledge scores at follow-up. Fisher’s exact test will be used to compare proportions of sufficient knowledge after counselling and at follow-up. Participants will be rated as having sufficient knowledge if they correctly answered at least 8 out of 12 questions. Unpaired t-tests will be used to compare average individual differences between planned and achieved values of blood pressure and HbA1c. Fisher’s exact tests will be used to compare the groups regarding rates of individual goal achievement (yes/no): statin choice, smoking status, blood-pressure (defined as reaching 80% to 120% of the goal), and HbA1c (defined as reaching 80% to 120% of the goal). Mann Whitney U-Test will be used to compare the medication uptake from T1 to T2 (increase/unchanged/decrease).

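### Medication change is scored from medical records at T1 and pill packages at T2, so disagreement between the two sources is coded as change and dilutes a secondary comparison

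*Protocol article*

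**What the plan says.** The Outcomes section lists "medication uptake from T1 to T2" as the fourth secondary outcome. Table 2 gives its source: variations in intake "are documented using medical records (T1) and by verifying" pill packages at T2. T1 is the end of the counselling session and T2 is the 6-month follow-up. The Data collection section repeats the package check for follow-up ("Current medication is monitored by verifying" packages). For the analysis, the Secondary outcomes section states: "Mann Whitney U-Test will be used to compare the medication uptake from T1 to T2 (increase/unchanged/decrease"). No check of packages at T1 is described, and no record-to-record comparison at T2.

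Blood pressure at T2 also has two possible sources. The first choice is a diary: "Current blood pressure values (mean of 2 weeks) are extracted from patient diaries". The fallback is: "If values are not available, blood pressure is measured before counselling by a nurse applying a standardised procedure". Both enter the same comparison with the patient's goal.

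**The concern.** A change score is interpretable only if both ends are measured in the same way. Here one end is a prescribing record and the other is what the patient has in hand. A drug that was on record at T1 but never taken is missing from the packages at T2 and reads as a decrease. A drug taken at T1 but not recorded reads as an increase. A true new start can be cancelled to unchanged if another recorded drug was never taken. The scored outcome therefore mixes real change over six months with a standing difference between prescribing and possession.

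At stake is how the medication result can be read. If the comparison is null, the trial could not tell whether the programme left medication use unchanged or whether measurement noise hid an effect. The within-arm rates of increase and decrease would also not be rates of behaviour change. Analysis cannot repair this later, because T1 packages that were never seen cannot be reconstructed.

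**Working it through.** **The plan's own figure.** The document gives no sample size or power for the medication outcome. The only stated calculation is for knowledge (Sample size section: difference 0.20, SD 0.4, two-sided 5%, 80% power). It reproduces. The normal approximation is 2 × (1.96 + 0.84)² × (0.4/0.2)² = 62.7, so 63 per group. The exact t-test gives 63.8, so 64 per group, with power 80.1%. For 15% dropout, 128/0.85 = 150.6, so 151, close to the stated 154. None of this depends on the medication source. I take 64 per arm from it as the analysed number.

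**Assumed inputs.** The document gives no rates of true change and no rates of record-package disagreement, so these are assumptions. True increase/unchanged/decrease is 30/60/10 in the programme arm and 10/80/10 in control. Disagreement q is the same in both arms.

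**Recoding at q = 0.2.**
- Spurious decreases only: decrease becomes d + q·u, and unchanged becomes u(1 − q). Programme arm: 0.10 + 0.2 × 0.60 = 0.22 and 0.60 × 0.8 = 0.48, with increase still 0.30. Control: 0.10 + 0.2 × 0.80 = 0.26 and 0.80 × 0.8 = 0.64, with increase still 0.10.
- True increases also lost: increase becomes i(1 − q) and the lost part moves to unchanged. Programme arm: 0.30 × 0.8 = 0.24 and 0.48 + 0.06 = 0.54. Control: 0.10 × 0.8 = 0.08 and 0.64 + 0.02 = 0.66.

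| Scoring | Programme inc/unch/dec (%) | Control inc/unch/dec (%) | Mann-Whitney power, simulated |
|---|---|---|---|
| Same source at both times | 30/60/10 | 10/80/10 | about 60% |
| 20% of unchanged scored as decrease | 30/48/22 | 10/64/26 | about 53% |
| As above, and 20% of true increases scored as unchanged | 24/54/22 | 8/66/26 | about 40% |

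Under the last model, power is about 49% at q = 0.1 and about 37% at q = 0.3. Spurious decreases alone at q = 0.3 leave about 51%.

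**A second assumed scenario.** True increase/unchanged/decrease is 30/65/5 against 10/80/10, with patients shifted one category down or up by mistake. Power is about 81% with one source. It is about 73% with 5% down and 2% up, 64% with 10% down and 5% up, and 52% with 20% down and 5% up.

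**Is a false arm difference created?** Under the null (10/80/10 in both arms), equal disagreement leaves simulated type I error at 0.043 to 0.052, which is nominal. If nobody truly changes, 10% false decreases plus 5% false increases make 10 + 5 = 15% of each arm look changed, equally in both. The error rate rises only when disagreement differs by arm. With 5% upward shifts in both arms, downward shifts of 5% against 10% give about 0.07, and 5% against 20% give about 0.29.

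**Blood pressure.** Bias in the mean arm difference = (nurse-minus-diary offset) × (difference between arms in the share without a diary). Equal shares give 0. With an assumed offset of 5 to 8 mmHg and an assumed 20-point gap, it is 5 × 0.2 = 1.0 to 8 × 0.2 = 1.6 mmHg. The document gives neither the offset nor the gap.

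**The case against.** The source switch is identical in both arms, and T1 records largely reflect prescribing from before the programme could act. The noise therefore works against the trial's own hypothesis and does not flatter it. The outcome is the last of four listed secondary outcomes. Statin goal achievement is read from medication boxes at T2, without the T1 record, so it is not touched. All of this stands, and it limits the weight of the point. It does not remove it: the article itself fixes the two sources and the change score, so this is not a detail left to a fuller document.

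Three stronger readings are tempting, and the document does not support them.
- A reader might infer that the source switch creates a false difference between arms. That needs disagreement to differ by arm, and nothing in the text says that it does.
- A reader might put the whole fall to about 40% power down to spurious decreases. Those alone give about 53%; the rest needs true increases to be lost as well.
- A reader might infer that blood pressure is biased because programme patients, who set blood pressure goals in their session, keep diaries more often. That is plausible, but diary availability is not given for either arm. Blood pressure is compared with a goal at T2, so no method difference is scored as change over time. The number of nurse readings is not stated, so the fallback cannot be called a single reading. The 80% to 120% goal band also absorbs most of a modest offset: for an illustrative goal of 140 mmHg it is ±28 mmHg (0.2 × 140).

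**Conclusion.** The point holds for medication, as a loss of precision and of meaning. Followed as written, the plan scores record-package disagreement as medication change in both arms. In the two assumed scenarios, power falls by between about 7 points (60% to 53%) and 29 points (81% to 52%) for disagreement of up to 20% downward. The size rests entirely on assumed rates; that disagreement is scored as change follows from the text alone. No arm bias is shown. The knowledge outcome and the 154 to be randomised are unaffected. For blood pressure, the text supports only this: two kinds of measurement are pooled at T2, and a bias would arise if diary availability differed by arm.

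**What to change.** Classify medication change from the same source at T1 and T2. Packages brought to both visits are preferable, because Table 2 names intake as the construct. The cost is asking patients to bring their packages to the counselling visit as well.

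The alternative is to compare the electronic patient record at T1 and T2, label the result as a change in prescribing, and report the T2 package check separately as adherence. The Setting section says that prescriptions are already documented in that record, so the cost is one further extraction. This version does not capture changes in taking. Enrolment began in March 2013, so for patients already past T1 without a package check it is the only same-source option. One rule should then be applied to everyone.

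For blood pressure, keep the present hierarchy and report by arm how many T2 values came from diaries and how many from nurse measurement. This costs one extra field on the form. Replacing the two-week mean by a clinic measurement in every patient would trade one limitation for another and is not needed here.

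### Numeracy is measured only after counselling but analysed as a patient characteristic, so its association with knowledge could be confounded by study arm

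*Protocol article*

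**What the plan says.** One of the additional aims in the Objectives is "to assess if patients presenting high numeracy levels achieve better knowledge than patients presenting low numeracy".

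The Outcomes text reads "Knowledge is captured by a standardised questionnaire consisting of 12 questions to assess" comprehension and expectations, "plus one question to assess" numeracy. Table 2 lists Knowledge as 13 items at T1 and T2. Its footnotes mark realistic expectations as "6 out of 13 questions of the knowledge test" and numeracy as "1 out of 13 questions of the knowledge test". The numeracy row is scheduled at T1 only. The time points are defined as "T1; at the end of the counselling session; T2; at 6 months follow-up".

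The baseline list under Data collection does not include numeracy.

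Under Secondary outcomes, "Participants will be rated as having sufficient knowledge if they correctly answered at least 8 out of 12 questions". The Sub-group analyses section splits participants into sufficient and insufficient knowledge and tests the split against numeracy (yes/no) with Fisher's exact test. It does not mention study arm.

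Under Study interventions, the intervention arm works through a decision aid at least a week before the session. In the session, patients assess their own heart attack risk and are given outcome probabilities. The control arm covers diet, exercise and stress.

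**The concern.** The numeracy objective asks whether people who handle numbers better end up with better knowledge. For that, numeracy has to be a property that the patient brings to the trial. As scheduled, it is a post-randomisation measurement, taken after one arm alone has spent a session, and at least a week of reading, on risk figures.

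Arm is then a potential common cause. It is designed to raise knowledge, and it may raise the numeracy answer. If it does both, numerate patients are over-represented in the arm with high knowledge, and an unstratified test shows an association even when numeracy makes no difference within either arm. The planned test cannot separate this from a true association, so one stated objective could be answered wrongly.

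**Working it through.** **1. The plan's own figure.** The Sample size section gives 70% versus 50% correct, SD 0.4, two-sided 5% level and 80% power. The normal approximation is n = 2 × (1.960 + 0.842)² × 0.4² / 0.2² = 62.8, so 63 per group. The t-test version gives 63.8, so 64, with power 0.801. Allowing for 15% loss, 128 / 0.85 = 151, against 154 stated. The planning figures reproduce. They concern the primary comparison; the article gives no figure for the numeracy association.

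**2. Sufficient-knowledge rates implied by the planning figures.** Assume independent items, 12 items, a cut-off of 8, and 70% or 50% correct per item (binomial upper tail):
- intervention: P(at least 8 of 12) = 0.724
- control: P(at least 8 of 12) = 0.194

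On these assumptions, arm is a very strong determinant of the sufficiency split.

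**3. Pooled association with no within-arm association.** Let q_I and q_C be the proportions answering the numeracy item correctly in the intervention and control arms, with equal arm sizes.
- P(sufficient | numerate) = (0.724 q_I + 0.194 q_C) / (q_I + q_C)
- P(sufficient | not numerate) = (0.724 (1 − q_I) + 0.194 (1 − q_C)) / (2 − q_I − q_C)

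Worked example, q_I = 0.7 and q_C = 0.5: (0.507 + 0.097) / 1.2 = 0.503, and (0.217 + 0.097) / 0.8 = 0.393. The odds ratio is (0.503 / 0.497) / (0.393 / 0.607), about 1.57.

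| q_I (assumed) | q_C (assumed) | Sufficient if numerate | Sufficient if not | Pooled OR |
|---|---|---|---|---|
| 0.5 | 0.5 | 0.459 | 0.459 | 1.00 |
| 0.6 | 0.5 | 0.483 | 0.429 | 1.24 |
| 0.7 | 0.5 | 0.503 | 0.393 | 1.57 |
| 0.8 | 0.5 | 0.520 | 0.345 | 2.05 |

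In every row the odds ratio within each arm is 1 by construction, so an analysis stratified by arm would return 1.

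**4. The item count.** Text and table agree: 12 + 1 = 13. What does not fit is 13 Knowledge items at T2 alongside a numeracy item collected at T1 only. The only stated scoring denominator is 12, in the sufficiency rule; the denominator of the mean score is not given. To bound what that could matter:
- If the numeracy item were scored and did not differ by arm, the planned difference would become 12 × 0.20 / 13 = 0.185. Power at 64 per group would be 0.74 with SD 0.4. With the SD rescaled it would be 0.75 to 0.80 (assumed numeracy success 0.3 to 0.7, item-score correlation 0 to 0.6).
- If T1 were scored on 13 items and T2 on 12, each as a percentage of items asked, the intervention-arm mean at T1 would be (12 × 0.70 + 0.3) / 13 = 66.9% to (12 × 0.70 + 0.7) / 13 = 70.0%, against 70% at T2. The artefact is 0 to 3 points.

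**The case against.** The strongest reply is that nothing in the article shows counselling to change the numeracy answer. Table 2 describes the item as a short general-population test, not a heart attack question. Without a shift, the pooled odds ratio is 1.0. That stands, and it is why the conclusion is that the result could be confounded, not that it is.

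A second reply is that the article does not say the arms are pooled, and an analysis plan may stratify. This has some force. However, the same section restricts the paired T1–T2 test to the intervention group by name and places no such limit on the Fisher test, so pooling is the natural reading. Stratifying also would not turn a T1 measurement into a baseline one.

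Three stronger readings are tempting, and the documents do not support them:
- **That text and table contradict each other on 12 versus 13 items.** They do not; the text itself adds the numeracy question to the 12.
- **That numeracy is correlated with a score containing it.** For one of 13 independent items of equal variance, that correlation would be √(1/13) = 0.28. But the planned test uses the sufficiency split, which requires that patients "correctly answered at least 8 out of 12 questions", so numeracy lies outside it.
- **That T2 scores fall by up to 1/13 = 7.7 points.** This needs every patient to be right on numeracy at T1 and T2 to be divided by 13 with an item never asked. No section states such a rule. Setting the figure against the 20-point planning difference would also compare a within-arm change over time with a between-arm difference at T1.

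**Conclusion.** The concern holds for the numeracy objective. Numeracy is a post-counselling measurement used as a patient characteristic, and the test as written does not account for arm. The possible size is a spurious pooled odds ratio of about 1.2 to 2.1. This assumes a shift from 50% to between 60% and 80% in the intervention arm, independent items at the planning rates, equal arms and pooling. With no shift there is no distortion.

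A reader might infer that the primary result is at risk too. That is not shown: the primary test compares arms at T1, where both complete the same form, and the stated sample size reproduces. The Table 2 mismatch at T2 and the unstated denominator of the mean score are matters of tidy-up. They could touch the paired T1–T2 test only if the two visits were scored on different items, which the article does not say.

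**What to change.** 1. Move the one-minute numeracy item to the baseline forms, before randomisation. At the latest it should come before the booklet is handed out, because the intervention booklet already carries risk information. Use that value in the numeracy analysis.
2. For patients already enrolled (the first in March 2013) who have only a T1 value, flag it. Analyse numeracy within arm or stratified by arm, for example with a Mantel-Haenszel test. Stratification removes confounding by arm, but within the intervention arm a T1 value may still partly reflect what the session taught, so report it with that caveat.
3. State that the mean knowledge score uses the same 12 non-numeracy items at T1 and T2, and align the Knowledge row of Table 2 with this.

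The cost is one item moved, one sentence on scoring, a table edit and a stratified test in place of a pooled one. The drawback is two measurement times for numeracy in the data set, which the flag and the stratification handle. No change to sample size or to the primary analysis is needed.
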